#### The acupuncture for arousal group

Based on basic treatment, the patients in this group will be treated with acupuncture alone. The positioning of acupuncture points refers to the national standard of the People’s Republic of China in 2021 (GB/T 12346-2021) “Nomenclature and location of meridian points” (GB/T 12346-2021 Nomenclature and location of meridian points [S]). The selected acupoints are bilateral GB20 (Fengchi), GB12 (Wangu), BL10 (Tianzhu), GV15 (Yamen), and GV16 (Fengfu).

Due to the inability of coma patients to sit autonomously, the family members or caregivers will cooperate to fix the patient’s head to take the sitting position. Local acupoints will be disinfected routinely, and Huanqiu brand 0.30 mm × 40 mm and 0.30 mm × 50 mm stainless steel millimeter needles will be used (Suzhou Acupuncture and Moxibustion Supplies Co. Ltd.). Among them, GB12, BL10, GV15, and GV16 use the twirling-reducing method to directly puncture 1 inch; GB20 points to the opposite side of GB20 points through the puncture 1.5 inches. Because the patient is comatose, Deqi is based on the sense of tightness in the hands of the doctor. Then, the BT701-l B-type electroacupuncture instrument (Shanghai Huayi Medical Instrument Co., Ltd.) will be connected, the sparse-dense wave will be selected, the current intensity is 0.4 mA (to the extent that the local impending muscle twitched with the frequency of the pulse but the naked eye did not see the twitching), and the wave will be energized for 20 min, 1 time/day, 6 times/week, and 4 weeks of treatment.

#### The rTMS group

According to the principle of Faraday’s electromagnetic induction, rTMS generates a magnetic field on the coil through a strong current, and then, the magnetic field penetrates the skull into the cerebral cortex without attenuation and causes a local microinduced current in the corresponding cortex, changes the membrane potential of the cerebral cortex, affects brain metabolism and neuroelectric activity, and thus causes physiological and biochemical reactions. Based on basic treatment, the patients in this group will be treated with rTMS alone. The specific operations are as follows.

First, all patients in the rTMS group will have their resting motor threshold (RMT) measured by a physical therapist who is not involved in the current study before the intervention. When the patient’s muscle is in a relaxed state, TMS will be used to stimulate the motor cortex. At least 5 of the 10 stimulations induce the minimum stimulation intensity required for the motor-evoked potential of the target muscle with an amplitude of more than 50 μv, which is the motor threshold we need. The patient will subsequently lie flat on the bed, and the light will be dimmed. The transcranial magnetic stimulation device (Magstim, United Kingdom, Rapid2) will be used, and the midpoint of the intersection of the two coils of the “8”-shaped coil will be placed in the dorsolateral prefrontal cortex corresponding to the scalp according to the international EEG standard, paying attention to the tangency with the scalp. The dorsolateral prefrontal lobe localization method: Use the International 10–20 system-based EEG electrode localization cap, and the “F3” mark on the localization cap is the position of the dorsolateral prefrontal lobe. (Anatomical localization: Taking the left side as an example, the parietal center (the midpoint of the line between the nasal root and the occipital bone) is the starting point, and a vertical line is made at 8 cm from the line with the nasal root, and the left dorsolateral prefrontal lobe is 6 cm to the left.) The parameters used will be as follows: output intensity of 80% of the motor threshold, frequency of 10 Hz, stimulation time of 2 s, string interval of 20 s, 20 min/time, 1 time/day, 6 times/week, and 4 weeks of treatment. All rTMS treatments will be performed by professionally qualified physical therapists. There is no sham rTMS in this study.

#### The acupuncture for arousal combined with rTMS group

Patients in this group will be treated with acupuncture for arousal and rTMS. First, the acupuncture for arousal treatment will be given. After treatment, rTMS treatment will be continued. The operation will be the same as above, with 1 time/day, 6 times/week, and 4 weeks of treatment.

### Criteria for termination of the study

The study will be terminated when the following situations occur: poor compliance of patients after enrollment and non-cooperation with experimental research; during the treatment, critically ill patients need to be transferred to other departments or hospitals for treatment; the patient’s immediate family members request to withdraw from the study.

### Outcome measures

#### Primary outcomes

Our main purpose is to observe the improvement in the level of consciousness in patients with a minimal conscious state after stroke, so we choose some common clinical behavioral assessment scales and brain function test items.

##### The GCS score

The most widely used consciousness assessment tool for patients with disturbances of consciousness (25, 26). The highest possible score is 15 points, indicating clear consciousness; a score of 9 points or above is defined as awakening, and a score of less than 8 points is defined as coma. The lower the score is, the more severe the disturbance of consciousness.

##### The CRS-R score

Patients’ recovery of consciousness is rated on six dimensions, namely, auditory, visual, motor, speech, communication, and arousal, with scores ranging from 0 to 23. The higher the score of CRS-R, the better the patient’s state of consciousness. According to research, the design of the CRS-R is especially suitable for identifying patients with vegetative states and a minimal state of consciousness (27–29). It includes evaluation indicators that the GCS does not have, such as visual tracking and visual positioning. The CRS-R scale can further divide the state of consciousness into MCS -, MCS+, and eMCS. MCS− includes object localization, visual pursuit or fixation, automatic motor behaviors, object manipulation, and localizing noxious stimuli. MCS+ includes the ability to follow commands, object recognition, comprehensible verbal expression and meaningful communication (30). eMCS includes the functional use of two different objects and functional interactive communication (31). Regarding outcome indicator, data collection should include not only longitudinal changes in the CRS-R score but also the specific temporal dynamics of clinically significant consciousness improvement. This is defined as the time for patients with MCS− to eventually improve to MCS+ or eMCS/patients with MCS+ to eventually improve to eMCS after treatment.

##### Detection of central nerve-specific protein and neuron-specific enolase

S-100B is an important index used to evaluate damage to brain nerves, and neuron-specific enolase (NSE) is a type of nerve damage-specific marker that is commonly used in the clinic. The levels of S-100B and NSE can indicate the degree of nerve damage.

##### Functional magnetic resonance imaging

Functional magnetic resonance imaging (fMRI) can reflect the changes in blood oxygenation (BOLD), blood flow changes, and other conditions in the functional areas of the brain and then evaluate brain function stereoscopically and intuitively. BOLD-fMRI imaging can reflect dynamic changes in the functional activity of the cerebral cortex through hemodynamic changes following neuronal activity. A 3.0 T superconducting magnetic resonance imaging system (Siemens) will be used to collect imaging data. The gradient echo plane imaging sequence will be used to collect BOLD-fMRI data. Resting-state functional MRI is acquired at the beginning of the scan, and the parameters are as follows: TR = 2,000 ms, TE = 30 ms, flip angle = 90°, FOV = 224 × 224 mm, matrix size = 64 × 64 mm, slice thickness = 3.5 mm, and slice number = 33 slices. BOLD-fMRI will be performed 30 min before the intervention (baseline period) and 30 min after the end of the 4-week intervention (end period).

#### Secondary outcomes

The secondary outcome measures of this study are the safety test items that can assess the patient’s health status and potential safety hazards. It mainly includes routine blood tests, routine urine tests, coagulation tests, electrocardiograms, liver function tests, and renal function tests. These test items can help researchers understand the health status of patients, detect and address possible health problems in time, and ensure the safety of research.

### Efficacy evaluation

#### The threshold of clinical improvement (Using the CRS-R scale as the reference standard)

Using the type of disturbance of consciousness in the CRS-R scale as the reference threshold for clinical improvement. The clinical significantly effective: Patients initially diagnosed with either MCS− or MCS+ who progress to eMCS following therapeutic intervention. The clinical effective: Patients initially diagnosed with MCS− who progress to MCS+ status following therapeutic intervention. The clinical ineffective: Characterized by either (a) patients initially diagnosed with MCS− who regress to vegetative state (VS) or maintain MCS− status following therapeutic intervention; or (b) patients initially diagnosed with MCS+ who regress to VS, MCS-, or maintain MCS+ status without further progression following therapeutic intervention.

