**Methods and analysis:**

This is a single-center design, randomized, controlled, third-party blind trial involving 117 patients. Three groups of patients will receive 4 weeks of treatment. Under basic treatment, the acupuncture for arousal group will only receive acupuncture treatment. The rTMS group only receives rTMS treatment; the combined group is treated with the acupuncture for arousal and rTMS. The main outcome indicators are the GCS score scale, the CRS-R score scale, central nerve-specific protein (S-100B), neuron-specific enolase (NSE), and functional magnetic resonance imaging (fMRI). The secondary outcome indicators are laboratory safety parameters, including routine blood tests, routine urine tests, coagulation tests, electrocardiograms, liver function tests, and renal function tests. Finally, the measurement data and enumeration data will be analyzed via SPSS 25.0 software.

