#### Awakening effective rate and awakening time (Using the CRS-R scale as the reference standard)

Awakening effective rate = The number of awakening cases in each group ÷ The total number of persons in each group × 100%. The number of awakening cases: The state of consciousness after treatment is improved compared with that before treatment. For example, patients initially diagnosed with MCS− who progress to either MCS+ or eMCS following therapeutic intervention, as well as patients initially diagnosed with MCS+ who progress to eMCS following therapeutic intervention. Awakening time is the point at which the patient exhibits improvement in the type of consciousness described above.

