### Sample size calculation

The GCS score was used as the primary outcome measure for the sample size calculation, following the method outlined by Lai Shilong in the Methodology of Clinical Research of Integrated Chinese and Western Medicine. Based on a study by Li Yuyuan et al. (25), the GCS score for the acupuncture combined with rTMS group was 10.30 ± 3.47 after 4 weeks of treatment. The GCS score for the acupuncture-only group was 8.33 ± 2.97, whereas that for the rTMS group was 8.16 ± 2.98. Taking *α* = 0.05, two-sided test, and *β* = 0.2, the ratio of the three groups of sample sizes was 1:1:1. After the above values are substituted with PASS 15 software, the sample size required for each group is calculated to be 32 cases. Considering a shedding rate of 20%, 39 patients are included in each group, and 117 patients are ultimately included in this study.

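### The categorical CRS-R efficacy grade pools patients who regress with patients who do not change, so no categorical consciousness measure can show deterioration by arm

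*Protocol article*

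**What the plan says.** The section on the threshold of clinical improvement defines three grades from the CRS-R category before and after treatment. The lowest grade takes in MCS− patients "who regress to vegetative state (VS) or maintain MCS− status following therapeutic intervention" and MCS+ patients "who regress to VS, MCS-, or maintain MCS+ status without further progression following therapeutic intervention".

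The next section, on the awakening effective rate and awakening time, defines an awakening case as one where "The state of consciousness after treatment is improved compared with that before treatment". Awakening time is the point at which that improvement appears. The time measure in the CRS-R score section is likewise a time to improvement.

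The grade is not on the list of declared main outcomes. The abstract states that "The main outcome indicators are the GCS score scale, the CRS-R score scale", followed by S-100B, NSE and fMRI. The sample size section adds: "The GCS score was used as the primary outcome measure for the sample size calculation". Both scales move with worsening. For GCS, "The lower the score is, the more severe the disturbance of consciousness". For CRS-R, "data collection should include not only longitudinal changes in the CRS-R score" but also the timing of improvement.

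The secondary outcomes are safety tests: "It mainly includes routine blood tests, routine urine tests, coagulation tests, electrocardiograms, liver function tests, and renal function tests". The Safety assessments section commits to recording all adverse events, including serious ones. The examples it gives are skin reactions, needle reactions, laboratory abnormalities, pneumothorax and needle-site infection, and it speaks of causality in relation to acupuncture only.

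**The concern.** The protocol foresees that patients may regress, names the transitions, and then puts them in one grade with stability. That is a stated rule, not a detail left to a fuller document. The trial aims to clarify both efficacy and safety in patients whose level of consciousness is the target of treatment. An arm in which some patients lose ground and an arm in which the same number simply stay put would receive the same categorical result.

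The other measures compensate only in part. GCS and CRS-R scores are summarised as means, in which a few falls can be offset by gains elsewhere. The adverse event record may catch a regression, but nothing in the article defines a fall in CRS-R category as an event or has it counted per arm.

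**Working it through.** **Step 1. Map each transition to its grade** (section on the threshold of clinical improvement).

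| Baseline | After treatment | Grade | Direction |
|---|---|---|---|
| MCS− | eMCS | significantly effective | better |
| MCS+ | eMCS | significantly effective | better |
| MCS− | MCS+ | effective | better |
| MCS− | MCS− | ineffective | same |
| MCS− | VS | ineffective | worse |
| MCS+ | MCS+ | ineffective | same |
| MCS+ | MCS− | ineffective | worse |
| MCS+ | VS | ineffective | worse |

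Of the five ineffective transitions, three are regressions and two are no change. On the awakening rate all five are non-events, and none has an awakening time.

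**Step 2. Illustrate the size.** The documents give no regression rate and state no figure to reproduce, so the counts below are assumed. Only the 39 per arm comes from the protocol (Sample size calculation).

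| | Significantly effective | Effective | Unchanged | Worsened | Total |
|---|---|---|---|---|---|
| Arm A | 12 | 8 | 19 | 0 | 39 |
| Arm B | 12 | 8 | 13 | 6 | 39 |

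- **Protocol's three grades.** Both arms become 12 / 8 / 19, because 19 + 0 = 13 + 6. The tables are identical, so any test gives p = 1.0. This would hold for any split of the 19 into unchanged and worsened.
- **Worsened count.** 0/39 against 6/39 = 15.4%. The two-sided Fisher p is 2 × C(39,6)/C(78,6) = 2 × 3,262,623 / 256,851,595 = 0.025. The difference is 15.4 percentage points, with a 95% Newcombe interval of about 3 to 30 points.
- **Rank test on four ordered grades.** Mann–Whitney U = 817.5 against 39 × 39 / 2 = 760.5 under no difference, giving p = 0.55.

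The rank test therefore stays far from significance even with the finer grades. The information lies in the separate count.

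**Step 3. What the primary scores would show.** If six of 39 patients each fall by d points on a scale, the arm mean moves by 6d/39 = 0.15d. An average gain of 6d/33 = 0.18d among the other 33 cancels it. The means register worsening, but do not show how many patients worsened.

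**The case against.** The strongest reply is that the grade is a responder definition, and a responder definition asks only who improved. It is not a declared main outcome. The main outcomes are GCS, CRS-R, S-100B, NSE and fMRI, and GCS drives the sample size. Both scales fall when consciousness worsens, so an arm with several regressions would have its mean pulled down. The Safety assessments section covers all adverse events, and the examples it lists do not limit that duty. The list of secondary tests is also open, since it is said to be what is mainly included. The counts in the illustration are invented, with equal improvement by construction.

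Most of this stands. A reader might infer from the grade that harm to consciousness is invisible in the trial's main efficacy result, or that no safety record could capture it. The documents support neither reading, for the reasons just given.

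What remains is narrower. The protocol goes beyond a yes/no responder rule: it offers a graded scale, names the regressions and then merges them with stability. A general duty to record adverse events does not oblige anyone to treat a fall in CRS-R category as one, or to tabulate it by arm. The causality wording refers to acupuncture alone, although one arm receives rTMS without acupuncture and another receives both.

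The primary scores also have a gap of their own. Transfer of a critically ill patient elsewhere is among the termination criteria, and missing data are filled by last observation carried forward. A patient who leaves after deteriorating may thus keep an earlier, better score.

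**Conclusion.** The point holds for the categorical measures. The grade, the awakening rate and the awakening time cannot distinguish a patient who regressed from one who did not change, and no named event count fills that gap. It does not extend to the primary GCS and CRS-R scores, which register worsening as group means, or to adverse event recording in general, which is broad enough to admit a regression without naming it.

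The transition map follows directly from the protocol's definitions and needs no assumption. The size rests wholly on assumed counts: 0 against 6 of 39 shows what the grade could conceal, not what is expected. The sample size and the primary comparison are unaffected. This is a free improvement in reporting.

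**What to change.** Split the ineffective grade into two: unchanged, and worsened, defined as any fall in CRS-R category from baseline (MCS− to VS, MCS+ to MCS−, MCS+ to VS). Report the number worsened per arm, with a confidence interval for the difference between arms, alongside the safety outcomes. The four ordered grades may be used in the rank test, but the separate count is the essential part.

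The cost is a change of wording and one more table row. The CRS-R category before and after treatment is already needed for the grade, so no visit, patient or assessment is added.

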#### Awakening effective rate and awakening time (Using the CRS-R scale as the reference standard)

Awakening effective rate = The number of awakening cases in each group ÷ The total number of persons in each group × 100%. The number of awakening cases: The state of consciousness after treatment is improved compared with that before treatment. For example, patients initially diagnosed with MCS− who progress to either MCS+ or eMCS following therapeutic intervention, as well as patients initially diagnosed with MCS+ who progress to eMCS following therapeutic intervention. Awakening time is the point at which the patient exhibits improvement in the type of consciousness described above.

### Sample size calculation

The GCS score was used as the primary outcome measure for the sample size calculation, following the method outlined by Lai Shilong in the Methodology of Clinical Research of Integrated Chinese and Western Medicine. Based on a study by Li Yuyuan et al. (25), the GCS score for the acupuncture combined with rTMS group was 10.30 ± 3.47 after 4 weeks of treatment. The GCS score for the acupuncture-only group was 8.33 ± 2.97, whereas that for the rTMS group was 8.16 ± 2.98. Taking *α* = 0.05, two-sided test, and *β* = 0.2, the ratio of the three groups of sample sizes was 1:1:1. After the above values are substituted with PASS 15 software, the sample size required for each group is calculated to be 32 cases. Considering a shedding rate of 20%, 39 patients are included in each group, and 117 patients are ultimately included in this study.

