Compared with other states of disturbance of consciousness after stroke, the incidence of MCS after stroke is high, and patients often need long-term monitoring and treatment to survive, causing great burden and huge economic pressure to society and families (23). In addition, there is no effective and standardized treatment for MCS, so it is of great economic and social significance to find a safe and effective wake-up method for MCS patients. Lam Ching et al. (24) reported that compared with Western medicine, acupuncture alone or plus rTMS, traditional Chinese medicine, traditional Chinese medicine combined with Western medicine were more effective in improving depression symptoms of patients with post-stroke depression. Among all therapeutic strategies evaluated, the combination of acupuncture with rTMS emerged as the most efficacious intervention modality, suggesting potential synergistic neuromodulatory mechanisms warranting further investigation in controlled clinical trials. Therefore, for patients with post-stroke disturbance of consciousness, we put forward the scientific hypothesis that acupuncture combined with rTMS can promote the improvement of consciousness in patients with MCS. This study will utilize acupuncture for arousal combined with rTMS to treat post-stroke MCS, conducting efficacy and safety evaluations to facilitate its future clinical application and to establish a standardized, effective treatment scheme for MCS. Meanwhile, through the detection of neural specific markers and brain functional magnetic resonance imaging, the mechanism of promoting the functional reorganization of brain regions will be discussed, which could provide a more scientific basis for the study of the wake-promoting mechanism of MCS in the future.

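### The 32 per group does not follow from the three quoted SDs (all three give 35), 39 leaves 31 after 20% loss, and the 80% power holds for the ANOVA only if nearly all 39 contribute full data

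*Protocol article*

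**What the plan says.** Under Sample size calculation the protocol states that "The GCS score was used as the primary outcome measure for the sample size calculation". The inputs come from one earlier study. For the combined arm, "the GCS score for the acupuncture combined with rTMS group was 10.30 ± 3.47 after 4 weeks of treatment". The single-therapy arms enter with a mean of 8.33 and SD of 2.97 (acupuncture) and a mean of 8.16 and SD of 2.98 (rTMS). Alpha is 0.05 on two sides, beta is 0.2, and allocation is equal. From these inputs, by PASS 15, "the sample size required for each group is calculated to be 32 cases". The next step allows for patients lost: "Considering a shedding rate of 20%, 39 patients are included in each group", which makes 117 in total. The paragraph names neither the test nor the SD that was entered.

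Under Clinical data analysis, the three groups are compared by one-way ANOVA and pairs of groups by a q-test. Under Statistical analysis, all analyses follow intention to treat, with last observation carried forward (LOCF) for missing data. The Introduction gives the hypothesis: "we put forward the scientific hypothesis that acupuncture combined with rTMS can promote the improvement of consciousness in patients with MCS".

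**The concern.** Three means and three SDs are offered as the basis of the calculation, so a reader should be able to recover 32 from them, and 39 from 32 and the 20%. Neither step works as described. Both errors run in the direction of too few patients.

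The paragraph also leaves open which comparison the 80% belongs to. All three arms receive active treatment, so a benefit of the combination can be seen only against the single therapies. The pairwise comparisons matter for interpretation, and no power is given for them. A non-significant pairwise result could then be read as evidence against the combination, on the belief that the trial had an 80% chance of finding the planned difference.

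**Working it through.** **Inputs** (Sample size calculation): means 10.30, 8.33, 8.16; SDs 3.47, 2.97, 2.98; two-sided alpha 0.05; power 0.80; equal groups; 20% loss.

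**1. Reproducing 32 with a one-way ANOVA.**
- Grand mean: (10.30 + 8.33 + 8.16)/3 = 8.93.
- Sum of squared deviations: 1.37² + 0.60² + 0.77² = 2.8298.
- Pooled variance: (3.47² + 2.97² + 2.98²)/3 = 29.7422/3 = 9.914, so SD 3.149.
- Noncentrality: λ = n × 2.8298/SD². Power is the probability that a noncentral F(2, 3n − 3; λ) exceeds its 5% critical value.

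| Common SD used | n per group for 80% | Power at 32 |
|---|---|---|
| 2.97 | 32 | 81.3% |
| 3.00 | 32 | 80.5% |
| 3.01 | 32 | 80.2% |
| 3.149 (all three pooled) | 35 | 76.3% |
| 3.47 | 43 | 67.4% |

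At SD 3.02 the answer is already 33. The arithmetic mean of the SDs (3.14) also gives 35. A large-sample chi-square version with the pooled SD gives 34.

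Two other routes reach 32. A two-sided t-test of combined against rTMS (difference 2.14) with SD 2.97 or 2.98 does so, again leaving out 3.47. A one-sided normal formula for combined against acupuncture (difference 1.97) with SD 3.149 does so too, but it contradicts the stated two-sided test.

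**2. The allowance for loss.** 32 × 1.2 = 38.4, rounded up to 39. But 39 × 0.8 = 31.2, so 31 remain. To keep 32 after 20% loss needs 32/0.8 = 40.

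**3. Power at the sizes that matter.** The unadjusted t-test uses the pair's SD: √((3.47² + 2.97²)/2) = 3.230 against acupuncture and √((3.47² + 2.98²)/2) = 3.234 against rTMS. For example, at 32 the noncentrality is 1.97/(3.230 × √(2/32)) = 2.44, giving 67.1%. The q-test figures come from simulating normal data with the three unequal SDs and reading the q-test as Student-Newman-Keuls; the protocol does not say which q-test it means.

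| Analysed per group | ANOVA (unequal-SD simulation to noncentral F) | q-test: vs acupuncture / vs rTMS | Unadjusted t-test: same order |
|---|---|---|---|
| 31 | 73–75% | 62% / 67% | 66% / 73% |
| 32 | 75–76% | 63% / 68% | 67% / 74% |
| 39 | 83–85% | 73% / 78% | 76% / 82% |

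Read as Tukey's test, the q-test gives about 55% / 63% at 32 and 65% / 73% at 39. Each figure is for one comparison taken separately.

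**4. What LOCF might do (assumption, not in the protocol).** Suppose the 20% lost carry forward baseline values with no group difference and the same SD. The differences shrink to 0.8 × 1.97 = 1.58 and 0.8 × 2.14 = 1.71. With all 39 counted, ANOVA power falls to about 65%, and t-test power to about 57% and 64%.

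**The case against.** The best defence is that the planned analysis is by intention to treat, so all 39 per group are kept and ANOVA power is 83–85%, above the target. That stands as a condition: a reader might infer that the trial simply lacks 80% power, and the documents do not support so flat a statement. The defence is not complete, however. The protocol itself expects 20% loss, carrying values forward adds no week-4 information, and the q-test against acupuncture stays at about 73% even with all 39.

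Second, 32 has a plausible origin: a single SD of 2.97 to 3.01 covers two of the three quoted values, and equal variances are the ANOVA's own assumption. That is fair, and 32 should not be called untraceable. But equal variances call for pooling the three SDs, not for dropping the largest, and the text says the quoted values were what was entered. The shortfall is 3 per group, about 4 percentage points of power. The error in the loss allowance is 1 patient per group, small by itself.

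Third, a reader might infer that the trial must beat both single therapies to succeed; unadjusted t-tests would both be significant in about 58% of trials at 32 and 68% at 39. The protocol sets no such criterion. Its hypothesis says only that the combination can improve consciousness. That the pairwise tests are needed is inferred from the all-active design, so those joint figures are not the trial's power. A single contrast of the combination with the mean of the other two arms would have about 85% power at 32, but none is planned.

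**Conclusion.** The point holds in limited form. From the protocol's own inputs, the planned ANOVA needs 35 per group, not 32, and 39 does not leave 32 after the stated loss. ANOVA power is about 73–76% at 31 or 32 evaluable per group, and above 80% only if all or nearly all 39 give undiluted week-4 data. The planned pairwise q-tests have about 62–68% power at 31 or 32, and 73% and 78% at 39.

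This rests on the ANOVA being the test that was sized (it is the planned three-group test, but the sample size paragraph does not say so), on normal data with the quoted means and SDs, and on Student-Newman-Keuls for the q-test. It should be fixed: the stated figures are wrong, but the correction is one of reporting and does not require more patients.

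**What to change.** Keep 117 patients and restate the sample size paragraph so that it:

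- names the test that was sized and the SD entered;
- states that a one-way ANOVA using all three quoted SDs (pooled 3.15) needs 35 per group for 80% power;
- states that 39 per group leaves 31 after 20% loss (and that keeping 32 would have needed 40);
- replaces the 80% claim with ANOVA power of about 73–75% at 31 and 83–85% at 39, the latter only if all 39 give week-4 data;
- says which q-test is meant and gives its power at the same sizes (as Student-Newman-Keuls, about 62% / 67% at 31 and 73% / 78% at 39 for combined against acupuncture / rTMS), marked as applying to each comparison separately.

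The q-test figures should be used here, since the unadjusted t-test figures overstate the power of the planned analysis. The cost is one rewritten paragraph and a less favourable stated power; recruitment, allocation and data collection do not change.
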